### Intervention in the control group

The patients will operate an Atmosphere air purifier in their bedrooms, but this air purifier will contain a placebo filter. This filter is also of a two-way design with an airflow velocity of 100/200 cubic feet/minute. Instructions will be given for the units to be left running continuously. The patients must stay in their bedroom at night for 4 weeks (> 8 h each day).

### Concomitant care and interventions

During the treatment and observation periods, participants will be prohibited from taking medications such as antihistamines, corticosteroids, decongestants, or leukotriene receptor antagonists orally or intranasally. Only patients with severe symptoms would be permitted to use anti-allergy agents. The type of medication, dose, and use will be recorded by the patient for analysis. For other complex chronic diseases, patients must continue taking their routine medications and therapies. Research staff will record the details of the diseases, medications, and therapies in the case report.

### Primary outcome measure

The visual analog scale (VAS) will be used to measure symptom severity and quality of life. The primary outcome measure is a difference in the VAS.

### Secondary outcome measures

The secondary outcomes will be changes in nasal symptoms, allergy symptom scores, Rhinoconjunctivitis Quality of Life Questionnaire (RQLQ) scores, Epworth Sleepiness Scale scores, and tolerability scores for the Atmosphere air purifier.

#### Nasal symptoms

The most important symptom is a swelling of the turbinates, which will be graded as 1 (“mild”), 2 (“moderate”), or 3 (“severe”).

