**Methods:**

This is a randomized, double-blind, clinical controlled trial that will test active and inactive versions of an air purifier (Atmosphere®; Amway China). Sixty AR patients sensitive to the allergens produced by *Artemisia* pollen will be assigned randomly to two groups of equal numbers. All patients will undergo a 4-week treatment period and a 4-week observation period. Evaluation will be conducted at baseline (day 0) and on days 7, 14, 21, 28, and 56. The primary outcome measure will be the difference in visual analog scale scores from baseline. Secondary outcomes will be changes from baseline in nasal symptoms, allergy symptom scores, responses to the Rhinoconjunctivitis Quality of Life Questionnaire, Epworth Sleepiness Scale scores, and tolerability scores for the air purifier. Side effects of treatment will be recorded.

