## Methods/Design

### Design

This is a randomised, double-blind, placebo-controlled clinical trial that tests active and inactive versions of an air purifier. The air purifiers are equipped with monitors to measure the number of hours they operate. AR patients sensitive to the allergens produced by *Artemisia* pollen will be assigned randomly to two groups of equal numbers. All patients will accept a 4-week treatment period and a 4-week observation period. Patient evaluation will be undertaken at baseline (day 0) and on days 7, 14, 21, 28, and 56 (Table 1). Figure 1 displays a flowchart of the study design. Specific tests that will be conducted at each follow-up occasion are outlined in Table 1.

**Table 1 Tab1:** Schedule of patient evaluation

Outcome measures	Screening stage	Remedial period				Observation period
	Baseline	Day 7	Day 14	Day 21	Day 28	Day 56
Nasal symptoms	X	X	X	X	X	X
Allergy symptom score	X	X	X	X	X	X
Visual analog scale score	X	X	X	X	X	X
Rhinoconjunctivitis Quality of Life Questionnaire	X	X	X	X	X	X
Epworth Sleepiness Scale score	X	X	X	X	X	X
Tolerability of the air purifier		X	X	X	X	
Treatment compliance		X	X	X	X	
Safety assessment		X	X	X	X	X

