## Follow-up

Upon completion of the 4-week treatment, patients will undergo a 4-week follow-up period. Research staff will continue to follow participants by telephone, short messaging via mobile telephone, or in the clinic. During the treatment period, follow-up will be conducted weekly. A record of symptom assessment and treatment compliance/changes will be maintained. If participants discontinue/deviate from the intervention protocols, research staff will record the reasons for the change. Such participants and their data will be excluded from the study.

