#### Allergy symptom scores

Allergy symptom scores will be used to grade symptoms as 0 (“no symptoms”), 1 (“mild symptoms”), 2 (“moderate symptoms”), and 3 (“severe symptoms”). The symptoms graded will be congestion, sneezing, nasal itch, rhinorrhea, eye itch, ear/palate itch, eye redness, and tearing.

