### Collection and management of data

Research staff is responsible for data collection. The baseline variables will be age, sex, highest education level achieved, dwelling environment, career, diagnosis, results of allergen examination, disease course, family history, VAS score, nasal symptoms, allergy symptom score, RQLQ score, Epworth Sleepiness Scale score, and tolerability of the Atmosphere air purifier. Participants will be required to record the intake of any medication during this study period.

Monitoring and management of data will be performed by a third party, which will build the study database and program settings. All data will be double-imported into an electronic database by two operators. Identified input errors will be corrected until there are no discrepancies in the database. Data organisation, data coding, range checking for data values, and data conversion to ensure quality will be the responsibility of the statistician.

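### Two secondary outcomes are badly fixed: purifier tolerability is a change outcome with no scheduled baseline, and the turbinate score has no grade for absent swelling

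*Protocol article*

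**What the plan says.** **Tolerability.** Four places in the protocol article bear on it.

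- Abstract, Methods: "Secondary outcomes will be changes from baseline in nasal symptoms, allergy symptom scores" opens a list that ends "and tolerability scores for the air purifier".
- Secondary outcome measures: a list of changes, here without the words *from baseline*, ends "Epworth Sleepiness Scale scores, and tolerability scores for the Atmosphere air purifier".
- Design, Table 1: the row "Tolerability of the air purifier" is marked on days 7, 14, 21 and 28. The baseline and day 56 cells are empty.
- Collection and management of data: the list of baseline variables ends "RQLQ score, Epworth Sleepiness Scale score, and tolerability of the Atmosphere air purifier".

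The instrument is five questions about the purifier, each scored 1 to 5.

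**Turbinate swelling.** The Nasal symptoms section names it as the most important symptom, "which will be graded as 1 (“mild”), 2 (“moderate”), or 3 (“severe"). Table 1 schedules nasal symptoms at baseline and at every later assessment to day 56. The next section begins differently: "Allergy symptom scores will be used to grade symptoms as 0 (“no symptoms").

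**The concern.** A change score needs a value at both ends. For tolerability, the schedule supplies none at the start, while two other parts of the article imply that one exists. Staff following Table 1 will collect no day-0 value. Staff following the baseline list will ask patients to rate a device they have not yet used. Either way, the outcome described in the abstract cannot be meaningfully analysed.

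For the turbinates, the lowest available grade is mild swelling. A patient whose swelling clears, or who never had any, must be called mild or left ungraded. The first choice hides improvement. The second creates missing values in the patients who are doing best on this item. If clearing is more common with the active filter, scoring cleared patients as mild pulls the comparison on this item towards no difference.

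**Working it through.** The article states no figure for either outcome, so the check is mainly a comparison of sections.

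**Tolerability**

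| Source | Baseline value? | Used as a change? |
|---|---|---|
| Abstract, Methods | implied | yes, from baseline |
| Secondary outcome measures | not stated | yes |
| Table 1 | no; days 7, 14, 21, 28 only | not stated |
| Collection and management of data | yes | not stated |

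1. The abstract and the baseline list need a day-0 value; Table 1 provides none. They cannot all be followed.
2. Adding a day-0 assessment to Table 1 would not solve this. The questions concern the purifier, and the intervention sections place its use in the 4-week treatment period. A day-0 answer would record expectation, not tolerability.
3. Both arms run the same model of purifier, one with a placebo filter, so on-treatment scores can be compared directly between arms. The data already scheduled are enough.

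**Turbinate grade**

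1. With true grade *g* from 0 (none) to 3, and cleared patients scored as mild, the recorded grade is max(*g*, 1).
2. Mild to none: true improvement 1 − 0 = 1; recorded 1 − 1 = 0.
3. Moderate to none: true 2 − 0 = 2; recorded 2 − 1 = 1.
4. Severe to none: true 3 − 0 = 3; recorded 3 − 1 = 2, a loss of one third.
5. Each patient with swelling at baseline who clears therefore loses exactly 1 grade. If a share *pA* of the active arm and *pC* of the control arm clear, and few patients in either arm start without swelling, the difference in mean change is understated by 1 × (*pA* − *pC*) grades.
6. The article gives neither share. The understatement is 0 if the shares are equal and grows by 0.1 grade for each 10 percentage points by which the active arm exceeds control. No value in that range can be preferred from the documents.
7. If cleared patients are left blank instead, step 5 does not apply. The problem is then missing data, and its size is also unknown.
8. The inclusion criteria in Table 2 do not require turbinate swelling, so patients with no valid grade at baseline are possible.

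**The case against.** **On tolerability.** Both outcome sentences can be read with tolerability as a separate final item, so that only the outcomes before it are changes. Table 1 fits that reading, and only the abstract says *from baseline*. This has force. But it leaves the baseline list in conflict with Table 1, and it leads to the same on-treatment analysis as the fix below. It is also fair that a baseline value is claimed in one section. The defect is therefore an inconsistency to reconcile, not proof that no baseline was ever intended.

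**On the turbinate scale.** The article is condensed, and the case report form may carry an option for none that is not visible here. That cannot be excluded. The section nevertheless sets out what reads as the full set of grades for this item, next to a scale that does start at 0.

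**Stronger readings that the documents do not support.**

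- The Discussion hypothesises that patients will be symptom-free in a pollen-free environment, so a reader might infer that the trial cannot detect the effect it expects. It can: the allergy symptom score has a grade for no symptoms and includes congestion, and the primary outcome is the VAS. Only one secondary item has the floor.
- The Follow-up section says "Research staff will continue to follow participants by telephone, short messaging via mobile telephone, or in the clinic", so a reader might infer that turbinate swelling would be graded remotely. No section says so. Clinic contact is one of the listed modes, and the Setting section places data collection in the outpatient department.

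**Conclusion.** Both points hold, and both are minor.

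- **Tolerability:** the change outcome cannot be computed from the assessments in Table 1, and the article contradicts itself on whether a baseline exists. This needs no numerical assumption.
- **Turbinate swelling:** as stated, the scale cannot record absence. The loss of 1 grade per cleared patient is exact if such patients are scored as mild. The effect on the arm comparison is unknown, because it depends on clearing rates that the article does not give.

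It would go too far to say that these outcomes fail altogether. On-treatment tolerability can be analysed as collected, and the turbinate score can still show movement between severe, moderate and mild. The primary outcome is untouched.

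**What to change.** **Tolerability.** Define the outcome as the on-treatment score compared between arms, choosing in advance either day 28 or the mean of days 7 to 28. Remove it from the baseline variables and from the change-from-baseline outcomes. Table 1 stays as it is. The cost is wording only.

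**Turbinate swelling.** Add grade 0 for none at all remaining assessments. For earlier patients, recode to 0 only where the source notes record normal turbinates, and do this without knowledge of allocation. Also report the score with grades 0 and 1 merged, so that early and late patients are on one scale.

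The cost is a small change to the case report form and a scale that changes part-way. The Trial status section reports 45 patients completed by the end of 2017, so at most 60 − 45 = 15 of the planned 60 could benefit from the new grade without recoding. For the others, a recorded 1 may mean none or mild unless the notes settle it. The merged analysis keeps the floor at mild and recovers none of the lost information; its purpose is comparability. The report should state this limit.

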#### Allergy symptom scores

Allergy symptom scores will be used to grade symptoms as 0 (“no symptoms”), 1 (“mild symptoms”), 2 (“moderate symptoms”), and 3 (“severe symptoms”). The symptoms graded will be congestion, sneezing, nasal itch, rhinorrhea, eye itch, ear/palate itch, eye redness, and tearing.

#### RQLQ

The RQLQ contains 28 questions covering seven topics (daily life activities, sleep, non-eye/nasal symptoms, practical problems, nasal symptoms, eye symptoms, and emotional status). The questions will be graded on a scale from 0 (“none”) to 6 (“very often/always”).

#### Epworth sleepiness score

The Epworth Sleepiness Score comprises eight questions about the patient’s sleepiness, which are scored from 0 (“none”) to 3 (“probably”).

#### Tolerability of the atmosphere air purifier

Tolerability measure of the Atmosphere air purifier is based on answers to five questions, which will be graded on a scale from 1 (“complete disagreement”) to 5 (“complete agreement”).

### Collection and management of data

Research staff is responsible for data collection. The baseline variables will be age, sex, highest education level achieved, dwelling environment, career, diagnosis, results of allergen examination, disease course, family history, VAS score, nasal symptoms, allergy symptom score, RQLQ score, Epworth Sleepiness Scale score, and tolerability of the Atmosphere air purifier. Participants will be required to record the intake of any medication during this study period.

Monitoring and management of data will be performed by a third party, which will build the study database and program settings. All data will be double-imported into an electronic database by two operators. Identified input errors will be corrected until there are no discrepancies in the database. Data organisation, data coding, range checking for data values, and data conversion to ensure quality will be the responsibility of the statistician.

### Statistical analyses

Statistical analyses will be carried out using SPSS v. 17.0 (IBM, Armonk, NY, USA) in the Clinical Evaluation Center of Southern Medical University (Guangzhou, China). Data will be described as the mean and standard deviation for normally distributed data, median and interquartile range for non-normally distributed data, and frequency and proportion for categorical data. All statistical inferences will be determined using two-sided tests. We will set a significance level of 0.05 and use 95% confidence intervals to measure the uncertainty of the estimate. Efficacy analyses will use last observation carried forward (LOCF) methodology to impute for cases not fully followed up during treatment. Pearson’s χ^2^ test will be used to compare the differences between the dropout rate and the dropout rate attributable to adverse events. Baseline data analyses (two sets) will include demographic indicators and general, primary, and secondary indicators before intervention. Measurement data will be compared using a paired *t*-test. For analyses of efficacy, for quantitative variables, comparisons between groups will be made by repeated measurement variance analysis and covariance analysis. For qualitative variables, comparisons between groups will be made using Pearson’s χ^2^ test, whereas central effects will be tested by a mixed-effects model. For rating variables, comparisons between groups will be made using the Kruskal-Wallis test. In terms of analyses of centre effects, the quantitative indicators will be tested by the general linear method, and the qualitative indicators will be tested by the Cochran-Mantel-Haenszel test methods. A logistic regression model will be used to evaluate and correct the rating variables.

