#### Sample size

The mean changes in findings before and after treatment were used as the indicator for efficacy evaluation in calculation of the sample size. We defined efficacy as changes in at least one score with the visual analog scale (VAS). Using a ratio of 1:1, α = 0.05, and 1 − β = 0.8 with a one-sided *t*-test, we calculated the appropriate trial sample size with 80% power. We found that a clinically significant difference could be detected using a sample of ≥21 patients in each group. We increased this number to 30 per group to allow for a predicted dropout rate of 30%.

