#### Rejection criteria and termination standards

Rejection refers to excluding patients from the analysis if they (i) do not meet the inclusion criteria; (ii) withdraw written informed consent; (iii) do not receive follow-up care after selection for the trial; (iv) violate the terms of the trial (such as by improper use of the air purifiers, leading to effects that cannot be evaluated).

Termination refers to censoring patients who have met the inclusion criteria but who halted their participation in the trial. Data from these patients will be included in the final statistical analyses. Termination standards include (i) symptoms (e.g., sneezing, runny nose, nasal obstruction, or nose itching) that become severe; (ii) the occurrence of a serious event, or (iii) other health reasons sufficient to halt participation in the study.

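### LOCF covers the treatment period only, while VAS is also scored at day 56; if the repeated-measures ANOVA includes day 56, treatment completers who miss it lose all their on-treatment scores

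*Protocol article*

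**What the plan says.** All references are to the protocol article.

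- **Design** separates two periods: "All patients will accept a 4-week treatment period and a 4-week observation period". The visits run through both: "Patient evaluation will be undertaken at baseline (day 0) and on days 7, 14, 21, 28, and 56". Table 1 marks VAS, nasal symptoms, allergy symptom score, RQLQ and Epworth at every visit, day 56 included.
- **Primary outcome measure** fixes no visit: "The primary outcome measure is a difference in the VAS". The Abstract defines the outcome as a difference from baseline, again with no visit named.
- **Statistical analyses** gives the only imputation rule: "Efficacy analyses will use last observation carried forward (LOCF) methodology to impute for cases not fully followed up during treatment". For quantitative efficacy variables, "comparisons between groups will be made by repeated measurement variance analysis and covariance analysis". The days entered are not listed. The software is SPSS 17.
- **Discussion** presents the four weeks of follow-up as serving an adequate evaluation of efficacy.
- **Rejection criteria and termination standards** says of patients who halt on health grounds: "Data from these patients will be included in the final statistical analyses". Table 2, by contrast, lists loss to follow-up among the exclusion criteria, and **Follow-up** removes patients who discontinue or deviate from the intervention, together with their data.

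**The concern.** The imputation rule stops where treatment stops, but the visit schedule does not. A patient with every score from day 0 to day 28 has been fully followed during treatment, so the LOCF sentence does not reach a missing day-56 value.

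Classical repeated-measures ANOVA, as in the SPSS GLM procedure, needs a complete row. If day 56 is one of its levels, one missing value after treatment removes four observed post-baseline treatment-period scores. Whether a patient's treatment result counts would then depend on an event after treatment ended. If LOCF fills all later visits for early losses, a patient lost at day 10 stays in on carried-forward values while a full completer is deleted.

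Two things are at stake: precision, and bias if patients who did badly are more likely to miss day 56. Such patients would come mostly from the placebo arm, so deleting them would shrink the estimated effect.

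**Working it through.** **1. The plan's own figure.** Sample size gives 21 evaluable per group and then says: "We increased this number to 30 per group to allow for a predicted dropout rate of 30" per cent. Check: 21 / (1 − 0.30) = 30 per group. Reproduced.

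**2. Implied effect.** No SD is stated, so the effect is recovered from the stated design. With n = 21 per arm, a one-sided t-test at α = 0.05 and 80% power, solving the noncentral-t power equation with noncentrality d·√(n/2) gives d = 0.78.

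**3. When patients are lost (assumption).** The article does not say how the 30% is spread over time. With a constant hazard over 56 days:
- hazard = −ln(0.70)/56 = 0.00637 per day
- lost by day 28: 1 − exp(−28 × 0.00637) = 16.3%
- lost between days 28 and 56: 30% − 16.3% = 13.7%, or 0.137 × 60 ≈ 8 patients

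**4. Rows left in a six-visit ANOVA.** Early losses are taken as kept through LOCF, so only late losses are deleted: 30 × (1 − 0.137) ≈ 26 per arm. With days 0 to 28 only, all 30 per arm remain.

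**5. Power at d = 0.78, α = 0.05 (two-sample t-test).**

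| n per arm | Two-sided | One-sided |
|---|---|---|
| 30 | 84% | 91% |
| 26 | 79% | 87% |

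Range: if one third to two thirds of the dropout falls after day 28, late loss is 10% to 20% (6 to 12 patients). That leaves 27 to 24 per arm and two-sided power of about 80% to 75%.

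**6. Bias if late loss depends on outcome (assumption).** Day-28 improvement was simulated with SD 1 in both arms and a true difference of 0.78. The probability of late loss followed a logistic curve in that improvement, with the intercept set so that 13.7% are lost overall. Among those remaining, the difference is:
- log-odds slope 1.0 per SD: about 0.71
- log-odds slope 1.5 per SD: about 0.67

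The slopes are not in the document. They show the direction and a plausible size, not an expected value.

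**7. The disposition rules side by side.** For a patient lost after day 28, Table 2 points to exclusion if the loss is for a change of address, telephone number or personal reasons. The termination rule points to inclusion if the patient halted for health reasons. Follow-up removes those who depart from the intervention, and does not clearly reach someone lost after the intervention ended. The LOCF sentence is silent on day 56.

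**The case against.** The strongest reply is that the deletion rests on a model the article never states. The days in the ANOVA are not given, and the LOCF sentence can be read to mean that efficacy is analysed over the treatment period, with day 56 as follow-up only. On that reading the rule and the analysis match and no score is lost. Covariance analysis is also named, and at a single visit it needs no complete row. Handling of a follow-up visit may also be left to an analysis plan that is not shown.

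Much of this stands: the loss is conditional. It does not dispose of the point. The article itself fixes a rule and a model, places day 56 in the same visit list, puts no visit limit on the outcome or the ANOVA, and ties the follow-up period to evaluating efficacy. The six-visit reading is therefore the natural one, though not the only one.

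Three stronger readings are tempting and not supported:
- **That late losses have no rule of any kind.** They have no imputation rule. Table 2 and the termination rule do bear on whether they are included, though not consistently.
- **That the analysis contradicts the termination rule outright.** The conflict arises only if day 56 is in the ANOVA and nothing is imputed there.
- **That power falls to 69%.** That is the two-sided figure at 21 per arm. It removes the early losses as well, which the plan says it will impute, and it also reflects planning with a one-sided test and analysing with a two-sided one, which is a separate matter.

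**Conclusion.** The point holds in conditional form. The stated scope of LOCF does not match the assessment schedule, and the visits in the repeated-measures ANOVA are not fixed. If day 56 is in the model, treatment completers who miss it are dropped with all their observed treatment-period scores. For patients halted on health grounds, this would sit badly with the rule that keeps their data.

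The cost is moderate: two-sided power of about 79% rather than 84%, with possible attenuation from 0.78 to about 0.71 to 0.67 SD. These figures assume constant-rate dropout over 56 days, early losses kept by LOCF, an effect inferred from the sample size rather than stated, and, for the attenuation, assumed slopes. If the model uses days 0 to 28 only, the cost is nil and a single clarifying sentence suffices. This is a cheap improvement, not a fatal flaw.

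**What to change.** In Statistical analyses, name the visits in the efficacy model and separate the two periods:

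- Analyse treatment-period VAS on days 0 to 28, so that a missing day-56 score removes no patient, and report day 56 as a separate off-treatment comparison.
- Alternatively, if day 56 stays in the same model, replace repeated-measures ANOVA with a likelihood-based mixed model with visit as a category, which uses all observed visits and needs no complete row.
- In either case, state that day-28 values are not carried forward to day 56, since that would enter an on-treatment score as an off-treatment result.
- Reconcile Table 2, the rejection and termination rules, and the Follow-up section, so that a patient lost after day 28 has one stated status in the analysis.

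The cost is a few sentences and, for the second option, SPSS MIXED in place of GLM repeated measures. No new data or patients are needed. The downside of separating the periods is that day 56 becomes a separate result with its own missing data.

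### LOCF is the only stated imputation for efficacy, with 30% dropout predicted and VAS likely to change over the weeks, so the VAS contrast can be biased in either direction

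*Protocol article*

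**What the plan says.** The Statistical analyses section of the protocol article fixes the method: "Efficacy analyses will use last observation carried forward (LOCF) methodology to impute for cases not fully followed up during treatment". It states no alternative and no sensitivity analysis. Quantitative outcomes are compared by repeated-measures analysis of variance and analysis of covariance.

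Dropout is expected to be substantial. The Sample size section first reports that "We found that a clinically significant difference could be detected using a sample of ≥21 patients in each group", then says "We increased this number to 30 per group to allow for a predicted dropout rate of 30" (per cent).

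Some dropout is tied to the outcome. Under Rejection criteria and termination standards, "Termination refers to censoring patients who have met the inclusion criteria but who halted their participation in the trial". Severe symptoms are one of the reasons listed, and these patients' data go into the final analysis. The same section rejects from the analysis patients who receive no follow-up after selection and those who withdraw consent. The Follow-up section says that participants who discontinue or deviate from the intervention are excluded together with their data.

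VAS is the primary outcome. Table 1 schedules it at baseline and at days 7, 14, 21, 28 and 56. No single visit is named as the primary time point.

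**The concern.** LOCF gives each incomplete patient the VAS of the last attended visit, as if nothing would have changed afterwards. The article's own hypothesis is that these patients have no symptoms without pollen, and Table 2 excludes patients sensitive to indoor allergens. VAS should therefore follow pollen exposure, and a flat course over four weeks is hard to defend.

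A patient stopped for severe symptoms can be scored at the milder value of the last weekly visit, so a failure is recorded as stable. If the purifier works, such patients may be more frequent in the control arm, which makes unequal dropout a realistic possibility.

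At stake is the primary contrast. It may be diluted, exaggerated or partly created by who left and when, and the imputed values enter the analysis with the same weight as observed ones.

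**Working it through.** **The plan's own figure.** 21 / (1 − 0.30) = 30 per group, so the stated size reproduces. At that rate 0.30 × 30 = 9 patients per arm would be incomplete. No SD is given, so the 21 cannot be checked. The 1-point effect used below as a yardstick is read from the efficacy definition in Sample size, whose wording is not fully clear.

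**Inputs from the article:** 30% predicted dropout; visits at days 0, 7, 14, 21 and 28.

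**Inputs assumed, because the article gives none:** the time course of VAS and of the effect; dropout by arm; dropout spread evenly over the last attended visits and unrelated to outcome; day 28 as the point of comparison.

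**Formula.** LOCF mean in an arm = sum over visits of (share whose last visit is v) × (mean at v).

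**1. True day-28 effect of 1.0, linear build-up (0, 0.25, 0.50, 0.75, 1), 30% dropout in both arms**
- Last visits at days 0 to 21: mean carried fraction (0 + 0.25 + 0.50 + 0.75)/4 = 0.375. Result: 0.7 + 0.3 × 0.375 = 0.8125.
- All dropouts have a day-7 value: mean carried fraction 0.50. Result: 0.7 + 0.3 × 0.50 = 0.85.
- Patients with only a baseline value rejected, as the article's rejection rule suggests: 1 − (0.225/0.925) × 0.50 = 0.88.

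**2. Other shapes, 30% dropout in both arms** (first figure with day-0 values carried forward, second from day 7 onward)
- Full effect from day 7: 0.7 + 0.3 × 0.75 = 0.925, or 1.00.
- Full at day 7, fading (1, 0.85, 0.70) to 0.5 at day 28: 0.35 + 0.3 × 0.6375 = 0.54, or 0.35 + 0.3 × 0.85 = 0.605. Both overstate the true 0.5.

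**3. No effect, common 2-point change over 28 days, dropout 20% against 40%.** False difference = trend × (1 − carried fraction) × difference in dropout.
- Days 0 to 21: 2 × 0.625 × 0.20 = 0.25.
- From day 7: 2 × 0.50 × 0.20 = 0.20.
- Baseline-only patients rejected: the imputed share is 0.75d/(1 − 0.25d). This gives 2 × 0.50 × (0.3333 − 0.1579) = 0.175.
- Equal dropout, or no trend: 0.

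On a rising trend the arm with more dropout looks better than it is; on a falling trend it looks worse.

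**4. Average over days 7 to 28 in place of day 28** (day-0 values carried forward). The complete course averages 0.625 of the day-28 value. Patients last seen at days 0, 7, 14 and 21 average 0, 0.25, 0.4375 and 0.5625, mean 0.3125.
- Linear effect, 30% dropout: (0.7 × 0.625 + 0.3 × 0.3125)/0.625 = 0.531/0.625 = 0.85.
- False difference as in step 3: 2 × 0.3125 × 0.20 = 0.125.

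**5. Simulation** (30 per arm, ANCOVA, two-sided 0.05, assumed change SD 1.286, between-visit correlation 0.7, day-0 values carried forward)
- Setting of step 3: type I error about 12% with LOCF, about 5% with observed day-28 values. With equal dropout, or no trend, LOCF also gave about 5%.
- Linear effect of 1.0, rising 2-point trend, dropout 20% active and 40% control: LOCF estimate 0.63 and power 47%, against 73% with observed values. With the dropout rates reversed the LOCF estimate is about 1.0, so the two biases cancel.

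**The case against.** The strongest reply is that each figure depends on inputs the article does not supply. That stands, and it rules out several stronger readings.

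- A reader might infer that LOCF necessarily shrinks a real effect. It does so if benefit grows over the four weeks. With full effect by day 7 there is little or no shrinkage, and a fading effect is overstated.
- A reader might infer that a false difference is to be expected. It needs a common trend and unequal dropout together, and the article states neither. Enrolment ran from 2016 onward, so one trend shared by all patients is not established.
- A reader might infer that the confidence interval is invalid in general. The simulated error rate stayed near 5% with equal dropout or no trend.
- A reader might treat day 28 as the endpoint and 30% as a ceiling. The article names no primary visit, and 30% is a prediction. Day 28 is the last treatment visit and LOCF is confined to the treatment period, so day 28 is a reasonable reading and no more.

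It is also fair that LOCF may reach far fewer than 30% of patients, given the exclusions under Follow-up and the rejection criteria. That does not defend the method; it shows that the sections disagree about whom it covers.

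Finally, sensitivity analyses and the recording of VAS at termination are details an article may leave to the full protocol or SAP, and their absence is not held against it. The choice of LOCF is different, because the article states it.

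**Conclusion.** The point holds as a conditional one. The article fixes LOCF as its sole stated imputation, predicts 30% dropout and keeps patients stopped for severe symptoms. Under these conditions the VAS contrast can be biased in either direction, and the documents do not allow the direction to be known in advance.

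The sizes are illustrations. About 0.81 to 0.88 of the day-28 effect is returned if benefit builds linearly and dropout is even and equal. That becomes 0.93 to 1.00 if the effect is full by day 7, and an overstatement if it fades. A false difference of about 0.18 to 0.25 points at day 28, or about 0.13 for the day 7 to 28 average, arises with a 2-point trend and 20% against 40% dropout. Against a planning effect read as 1 point, that is large enough to justify changing the method. The plan should be changed, but the article does not show that the result will be wrong.

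**What to change.** Before unblinding:

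1. Replace LOCF in the primary VAS analysis with a mixed model for repeated measures on observed VAS at days 7, 14, 21 and 28, with arm, visit, arm-by-visit, baseline VAS and baseline-by-visit.
2. Keep LOCF as a labelled sensitivity analysis.
3. Add a sensitivity analysis that gives patients terminated for severe symptoms a prespecified unfavourable VAS, for example the worst observed value. The mixed model assumes data are missing at random, which may fail for these patients, so it does not cure that problem alone.
4. Reconcile Rejection criteria and termination standards, Follow-up and Statistical analyses on whether patients who discontinue are analysed or excluded. Until this is done it is unclear whom any missing-data method covers.

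Cost: a different SPSS procedure and slightly more analysis work. The weekly VAS is already collected, so no new data are needed. The plan mentions a mixed-effects model only for centre effects, so the VAS model has to be written out. Recording VAS at the moment of termination is not part of this fix: it would be new data collection, and it could not be recovered for terminations that have already happened (45 patients had completed the study by the end of 2017).
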